## Abstract

**Background:**

Cardiovascular diseases (CVD) are leading causes of mortality and morbidity among Indigenous people in New Zealand, Australia and Canada and are a major driver of the inequities in life expectancy between Indigenous and non-Indigenous people in these countries. Evidence-based pharmaceutical management of CVD can significantly reduce mortality and morbidity for persons diagnosed with CVD or for those at intermediate or high risk of CVD. Health literacy has been identified as a major barrier in the communication and implementation of appropriate pharmaceutical management plans for CVD. Addressing health literacy is particularly relevant in Indigenous populations where there are unique health and adult literacy challenges.

**Methods/design:**

This study will examine the effect of a customized, structured CVD medication programme, delivered by health professionals, on the health literacy of Indigenous people with, or at risk, of CVD. Primary outcomes are patient’s knowledge about CVD medications; secondary outcomes examine changes in health literacy skills and practices. The study will employ a multi-site pre-post design with multiple measurement points to assess intervention efficacy. Participants will be recruited from four Indigenous primary care services in Australia, Canada and New Zealand. Three educational sessions will be delivered over four weeks. A tablet application will support the education sessions and produce a customized pill card for each participant. Participants will be provided with written information about CVD medications. Medication knowledge scores, and specific health literacy skills and practices will be assessed before and after the three sessions. Statistical analyses will identify significant changes in outcomes over each session, and from the pre-session one to post-session three time points.

**Discussion:**

This study will make an important contribution to understanding the effect of a structured primary care-based intervention on CVD health literacy in Indigenous populations. The study also illustrates the incorporation of Indigenous health research principles and processes in clinical trials and provides insights that may be useful in other contexts.

**Trial registration:**

Australian and New Zealand Clinical Trials Register (ACTRN12612001309875; date of registration 18/12/2012).

## Background

Cardiovascular diseases are major causes of mortality and hospitalisation for adult Indigenous peoples. Significant inequalities in CVD morbidity, mortality and the prevalence of cardiovascular disease risk factors between Indigenous and non-Indigenous populations have been documented in Australia [1] Canada [2], and New Zealand [3,4]. Explicit evidence-based guidelines for the management of CV risk factors and CVD have been available for many years. Healthy nutrition, exercise, smoking cessation, and medications are the key strategies of primary and secondary prevention. Initiatives such as explicit evidence-based CVD management guidelines [5], health provider education [6] and computerised decision support tools [7-11] have been implemented to assist health professionals and health services to provide high quality CVD care. However, CVD are chronic diseases and as such, the patient and their family are the primary ‘managers’ of these diseases. Self-management is central to effective CVD management [12]. A complex array of skills, knowledge and psycho-social factors influence a person’s ability to be an effective self-manager of chronic conditions [13]. Knowledge about CVD risk factors and medications is essential to self-management. Published literature on patients’ knowledge focuses on CVD risk factors and understanding of CVD risk assessment rather than knowledge and understanding of medications and their use [14-18]. Available evidence suggests that intermittent and non-adherence with medications is common and is associated with worse outcomes, including poorer control of risk factors, increased hospitalisations, morbidity and mortality [19-22].

Health literacy, defined as “the ability to access, understand and act on information for health” [23], is an important contributor to knowledge, self-management, and health outcomes generally [24-30] and for CVD [31]. The Institute of Medicine has reported that differences in health literacy alone account for 25–30 per cent of ethnic differences in health outcomes [32]. International surveys have found that the majority of the population in Australia, Canada and New Zealand (NZ) have inadequate levels of health literacy to effectively engage in health care. In NZ, Māori have higher health literacy needs than non-Māori [33,34]. While rigorous population based Indigenous data are lacking in Australia and Canada, the situation for Indigenous peoples in both countries is likely to be similar to New Zealand given the known inequities in health and education [35].

The intervention used in this trial was designed during a developmental phase. This included in-depth interviews with community members who were taking CVD prevention medications to ascertain their knowledge about their medications, what they would like to know about these medications, and how they would like to be provided with this information. There were significant knowledge gaps at all four locations and, while there was some locality variation, the knowledge gaps and expressed information needs were remarkably similar across sites. The data from these interviews were used to develop the intervention. Interviews with health professionals were also undertaken and explored their awareness and understanding of health literacy and how they addressed health literacy in their practice. Environmental scans have assessed the baseline health literacy demands the health service environment places on its clients. Data from health professional interviews and environmental scans will allow assessment of whether changes in health professionals’ awareness, knowledge and practices and changes in the health literacy environment may contribute to the results of the intervention trial.

### Study aims

The aim of this study is to test the effect of a customized, structured CVD medication programme, delivered by health professionals, on the related health literacy of Indigenous people with, or at risk, of CVD. Primary outcomes are patient’s knowledge about CVD medications. Secondary outcomes examine changes in health literacy skills and practices. The programme will be implemented in Indigenous primary health care services in Australia (one service), Canada (one service with two sites), and NZ (two services). The intervention will be delivered by nurses in NZ and Canada, and a researcher/health educator in Australia.

## Methods and design

The intervention trial utilizes a single arm pre-post design with multiple measurement points. Two factors related to the size of the local Indigenous communities preclude the use of randomised, controlled trial design. Firstly, there is a high likelihood of contamination between control and intervention groups in the Indigenous communities where the trial will be located. Secondly, the use of a control group is not feasible in these communities because the eligible population is relatively small and, in order to have sufficient participants receiving the intervention, all eligible people will have to receive it. The uniqueness of local Indigenous communities and their health services precluded the use of quasi-experimental design with matched primary care service controls located elsewhere.

### Indigenous community engagement in the research process

In keeping with ethical requirements and evidence based best practices for Indigenous research [36-39], as well as some site’s own research policies [40,41], the participating Indigenous communities have been involved in the development of the project from its inception.

The principal investigators in all three countries are Indigenous peoples and all the Indigenous researchers have pre-existing relationships with the participating Indigenous health services where the research will be based. These services were involved in all aspects of project development including decisions to submit a grant application, development of the application, study design, and the implementation of phase one of the project. Key staff from the health services are project co-investigators, and the intervention will be delivered by Indigenous staff employed by the health services. In all three countries specific policies and processes regarding project governance and implementation; health service provider/community expectations; benefits of the research; ownership, control, and access to research information, and dissemination of project results, including academic publications, have been agreed.

### Ethics

The study design and implementation processes were reviewed and approved by each of the four participating Indigenous health services. The study was approved by the Health and Disabilities Ethics Committees in NZ (MEC/10/061/EXP), the Human Research Ethics Committee (HREC) at the University of Melbourne, Australia and the Saint Michael’s Hospital Research Ethics Board, Toronto, Canada. The study was registered with the Australian and New Zealand Clinical Trials Register on 18th December 2012 (ACTRN12612001309875).

### Study locations

The study will be implemented in four Indigenous health services (five sites) across the three countries. In NZ, one service (Te Hononga o Tamaki me Hoturoa) is located in a large metropolitan city that provides nurse-led services but does not provide primary medical care services. Participants from this service will be drawn from nurse-led programmes for people with long-term conditions and for people recently discharged from hospital with a diagnosis of a CVD event. The second NZ site is located in a remote rural area whose health services are provided by Ngati Porou Hauora, an Indigenous health provider that delivers a range of primary care services including medical services.

The Australian partner is the Victorian Aboriginal Health Service (VAHS). VAHS is an urban community controlled Aboriginal health service that was established in 1973 to address the specific medical needs of local Victorian Aboriginal communities. VAHS now provides a comprehensive range of medical, dental and social services and supports the well-being of the community through contributions to community events and activities.

The Canadian study partner is the Dedwadadehsnye > s Aboriginal Health Access Centre (DAHAC), a provincially funded urban Indigenous health service which provides primary health care, traditional healing and health promotion programs to Indigenous people living in the cities of Hamilton and Brantford, Ontario. Recruitment and intervention will occur at both DAHAC sites, which are 40 km apart and have similarly structured primary health care services.

### Recruitment

Medical records at the sites will be systematically searched to identify potentially eligible patients. These patients will be contacted by a health service staff member who is not directly involved in the project and asked if they would like to know more about the trial. Patients who accept this invitation will then be contacted by the nurse/health educator who will provide information about the study and undertake formal consent procedures with patients that agree to participate. Participants will be able to invite family members to sit in on the sessions; however, data will not be collected from family members.

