### Eligibility

Patient participants are eligible for the trial if they are Indigenous adults ≥ 20 years of age and are enrolled with the participating health services. In addition they need to have been diagnosed with angina pectoris, myocardial infarction, transient ischaemic attacks or stroke OR (for Canada and Australia only) were known to be at risk of a CVD event and receiving medication to manage this risk. In Australia these participants were eligible if they were at high risk (≥15 % risk of a CVD event in the next five years) [36]. In Canada participants were eligible if they were assessed as having at least internediate risk (≥15 % risk of an event in the next 10 years) [42,43]. Finally, all participants need to be taking at least two of the following types of medicines: a statin, aspirin, a beta blocker, or an ACE inhibitor. Eligible participants will be excluded from the trial if they have a condition which means they are unable to provide informed consent or they have a cognitive deficit that interferes with their ability to participate in the intervention.

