### Statistical analyses

Descriptive statistics will describe the baseline characteristics of study participants (age, sex, CVD diagnosis, co-morbidities, medications), baseline blood pressure and lipid measures, and the characteristics of the sessions with respect to location (home/office) and whether or not family members were present. Finally we will describe the baseline health literacy skills and practices of participants including how and from where/whom they acquire information CVD medications.

To assess the effect of the intervention on patient knowledge about their medication we will examine the mean knowledge scores for each of the four CVD medication groups over time. We will test changes in mean scores from pre session one (T1) to post session three (T6). Baseline characteristics of participants who enrolled but did not complete the study will be compared to participants who finished the intervention to examine whether drop out was determined by specific characteristics or not.

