The study design also illustrates one approach to implementing clinical trials in distinctive local contexts. In Canada, networks of friends and family have been identified by members of our research team as the most important source of health information in diverse local Indigenous communities [47]. Furthermore, the relatively small population sizes of these communities means that, in order to have a sufficient sample to assess the effect of the intervention, it will have to be delivered to all eligible people in the health services. The study design needs to accommodate both these challenges, making a single arm, pre-post design with case studies of the surrounding environments for factors that may influence the effect of the trial, the most suitable design. Similar challenges may be encountered in other studies that are located in relatively small, local populations.

A key audience for our study results will be the Indigenous health service providers who are responsible for providing care to the patients in the study. We will work with these health service provider partners to interpret the study findings and identify recommendations for their practice. We will also share our study findings more broadly with Indigenous and non-Indigenous health policy makers, practitioners, and researchers.

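### The contamination used to rule out a control group can also reach the single-arm baseline: some later enrolees may be taught before T1, and nothing listed would show it

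*Protocol article*

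**What the plan says.** Methods and design gives two reasons for having no control group. The first is that "there is a high likelihood of contamination between control and intervention groups in the Indigenous communities where the trial will be located". The second is that the eligible population is small, so that "all eligible people will have to receive it". The Discussion presents the single-arm pre-post design as the most suitable way to accommodate these problems and, for Canada, reports that "networks of friends and family have been identified by members of our research team as the most important source of health information".

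Recruitment then opens the teaching to relatives: "Participants will be able to invite family members to sit in on the sessions; however, data will not be collected from family members". Under Intervention, each participant also receives a booklet.

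Eligibility lists two exclusions, inability to consent and an interfering cognitive deficit. Having already sat in on a session is not one of them. The baseline items under Measurement instruments and Statistical analyses do not include earlier attendance. Family attendance appears only as a descriptive feature of the index participant's session: "whether or not family members were present". The knowledge analysis tests the change in mean score from T1, before session one, to T6, after session three.

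**The concern.** In a single-arm pre-post design the comparator is the participant's own T1 score. Contamination that would reach a control group can equally reach a person who has not yet enrolled. The protocol applies the argument to the first case and not to the second.

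The route is specific. Because the whole eligible pool is to be treated, an eligible relative who sits in is also a likely later participant. That person's T1 would be entered as an untaught baseline. If the exposure is not recorded when it can be asked about, no later analysis can find it. At stake are the size of the estimated change, power where the true effect is small, and comparisons between sites or countries if exposure is uneven.

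**Working it through.** **1. Reproduce the plan's figures.** Power analysis gives 52 participants for an effect size of 0.4 and 90 for 0.3, with power 0.8 and alpha 0.05. A paired t-test on the change (noncentral t, n − 1 degrees of freedom, noncentrality d√n, two-sided alpha 0.05) needs:
- d = 0.4: n = 52 (power 80.8%; 51 gives 79.99%)
- d = 0.3: n = 90 (power 80.4%; 89 gives 79.9%)

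Both figures reproduce exactly and are not in dispute.

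**2. Model for a partly taught baseline.** Let p be the share of participants exposed before T1, and c the share of the full effect that they already hold at T1 and do not gain again by T6. Then

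observed effect = d × (1 − p × c).

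The document gives neither p nor c, so every value below is an assumption. The SD of the change is held at 1. Allowing for the extra spread between exposed and unexposed people lowers the power figures below by 0.2 percentage points or less for c = 0.5, and by 0.8 or less for c = 1.

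**3. Power at the recruitment targets** (100 at each NZ site and in Australia, 120 at each Canadian site; full recruitment and completion):

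| d | p | c | Observed effect | Power, n = 100 | Power, n = 120 |
|---|---|---|---|---|---|
| 0.3 | 0 | – | 0.30 | 84.4% | 90.3% |
| 0.3 | 10% | 0.5 | 0.3 × 0.95 = 0.285 | 80.6% | 87.2% |
| 0.3 | 20% | 0.5 | 0.3 × 0.90 = 0.27 | 76.2% | 83.5% |
| 0.3 | 30% | 0.5 | 0.3 × 0.85 = 0.255 | 71.4% | 79.1% |
| 0.3 | 20% | 1 | 0.3 × 0.80 = 0.24 | 66.2% | 74.2% |
| 0.4 | 0 | – | 0.40 | 97.7% | 99.2% |
| 0.4 | 20% | 0.5 | 0.4 × 0.90 = 0.36 | 94.6% | 97.4% |
| 0.4 | 30% | 0.5 | 0.4 × 0.85 = 0.34 | 92.0% | 95.9% |
| 0.4 | 20% | 1 | 0.4 × 0.80 = 0.32 | 88.7% | 93.5% |

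**4. Tipping point.** With n = 100, 80% power needs an observed effect of 0.283. For d = 0.3 that allows p × c up to 1 − 0.283/0.3 = 0.06. For d = 0.4 it allows up to 1 − 0.283/0.4 = 0.29.

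**5. Direction.** The formula assumes that pre-taught people gain less by T6. That is plausible for a bounded score and standardised content delivered three times, but the document does not show it. If their T6 rose by as much as their T1, the change would not move.

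**The case against.** A reader might infer that the T1 to T6 change is biased downward. The document does not support that. It states no enrolment order (staggering is a fair inference from individual sessions and 100 to 120 people per site), no count of related eligible participants and no measure of what an observer learns. The same tools are used six times, and practice, secular change or regression to the mean may push an uncontrolled change upward.

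A reader might also infer that power drops to 72% or 67%. Those values arise at the minimums of 52 and 90 (effects of 0.36 or 0.27, and 0.34 or 0.255), not at the targets. Pooled by country, NZ (200) and Canada (240) would keep about 95% and 98% power even at 0.255.

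Several limits on spill-over stand:
- Sessions cover only the index participant's own medication classes. Everyone must take at least two of the four, so two people share none only if each takes exactly two and the pairs are complementary. Some overlap is likely, but it is partial.
- The pill card shows one person's own medicines and is a weak vehicle.
- Many guests will not meet the eligibility criteria.
- The statement about family networks is made for Canada only.
- Attenuation on its own cannot create a false claim of benefit.

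It can also be said that a baseline form item is detail that an article leaves out, and that the protocol never claims its design removes all contamination. This weakens the point without removing it. The article itself states the contamination premise, the open sessions, the exclusions and the sole comparator, and an exposure not recorded before T1 cannot be recovered by a later analysis plan.

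**Conclusion.** The point holds as a possibility that the protocol's own text creates and does not guard against: some T1 scores may not be untreated, and the T1 to T6 change may be attenuated. The size is unknown, because it rests on p and c. The net sign of all biases in the uncontrolled change is also unknown.

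Under the illustrative p = 20% and c = 0.5, the estimate shrinks by 10%. The power loss matters mainly for an effect of 0.3 at a site of 100, which includes Australia, where the site is the whole country sample. At 0.4 it is minor. The case for acting is that the safeguard is cheap and must be in place before T1, not that harm has been shown.

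**What to change.** 1. At T0 or T1, before any testing, ask whether the participant has attended another participant's session or used another participant's booklet.
2. Where practical, take T1 from eligible members of the same household before any of them is taught. The knowledge tools are now planned for immediately before each session, so first sessions would need to be close together, or the timing rule would need a stated exception.
3. Report the T1 to T6 change without exposed participants as a sensitivity analysis beside the all-participant result.

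Family attendance need not change.

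The cost is one extra item and some scheduling work. The unexposed subset will be smaller, self-reported and non-random, so it supports the main result and does not replace it. A trend of T1 score on enrolment date could be shown as exploratory only, since it also reflects service change, case mix and assessor drift and cannot isolate contamination.

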### Eligibility

Patient participants are eligible for the trial if they are Indigenous adults ≥ 20 years of age and are enrolled with the participating health services. In addition they need to have been diagnosed with angina pectoris, myocardial infarction, transient ischaemic attacks or stroke OR (for Canada and Australia only) were known to be at risk of a CVD event and receiving medication to manage this risk. In Australia these participants were eligible if they were at high risk (≥15 % risk of a CVD event in the next five years) [36]. In Canada participants were eligible if they were assessed as having at least internediate risk (≥15 % risk of an event in the next 10 years) [42,43]. Finally, all participants need to be taking at least two of the following types of medicines: a statin, aspirin, a beta blocker, or an ACE inhibitor. Eligible participants will be excluded from the trial if they have a condition which means they are unable to provide informed consent or they have a cognitive deficit that interferes with their ability to participate in the intervention.

